## 3. Sample Size and Data Analysis Considerations

As recommended for pilot projects [92], we did not power the study for effect sizes at certain *p* values due to the large confidence intervals around effects in smaller samples. Instead, the primary objective of the REACH treatment development project is to establish acceptability/feasibility and specify study procedures in preparation for a *future* fully-powered clinical trial [92]. However, a preliminary power analysis is provided below as a guide for a future large-scale clinical trial should the pilot project prove successful. In order to have an 80% power to detect group differences at a two-tailed alpha level of .05 over 3 time points, a small treatment effect (f = 0.10) would require a total *n* = 526, a medium effect (f = 0.25) would require *n* = 86, and a large effect (f = 0.40) would require only n = 36. Clinically meaningful effect sizes on symptom outcomes (BPRS) are expected to be medium to large in magnitude and should place future sample size requirements in a feasible range. We should be able to gauge relevant treatment parameters with an open trial sample of 20 and a pilot RCT sample of 50. This will require recruitment of approximately 3–4 patients per month into study, which is feasible based on the admission rate at our study site and the recruitment rate achieved by the investigators in their previous studies.

We will examine effect size standard errors, confidence intervals, and clinically meaningful statistics (e.g., “number needed to treat”) as recommended for treatment development trials [93]. Furthermore, we will examine patterns of missing data and explore multiple methods for imputing data to determine consistency of results (maximum likelihood estimation, multiple imputation, and “worst case” scenario). If baseline differences are identified and associated with outcomes, these variables will be used as covariates in subsequent analyses. For example, history of illness (e.g., first episode versus chronic psychosis) may be important to examine due to its relationship with outcome in schizophrenia [94].

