Regarding treatment feasibility/acceptability, we will assess attrition rates and reasons for drop out. We also will assess levels of treatment acceptance and satisfaction (CSQ-8). Similar to other studies in this area [95,96], the primary outcome will be change on the BPRS total scale. Secondary outcomes will include symptom subgroups (e.g., positive, negative, mood), overall response rates (≥30% reduction [97] on BPRS), psychosocial functioning and quality of life, and rehospitalization rates. We also will examine potential predictors of outcomes to identify moderators and mediators that could be tested in subsequent research, including demographics, treatment adherence, and the proposed ACT-IN treatment mechanisms (AAQ-II, CAMS-R, VQ).

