Given all patients will be receiving appropriate pharmacotherapy as part of their hospital stay, we expect that both groups will show significant improvement in symptom severity by discharge. However, we also are interested in examining whether ACT provides certain advantages in terms of its impact on nonpsychotic symptoms (e.g., mood symptoms) or other outcomes (e.g., psychosocial functioning) compared with eTAU. Consistent with the analyses we would plan to conduct in a future full-scale RCT, we will generate multilevel linear models in a preliminary fashion to examine whether treatment condition, time, and the treatment condition X time interaction predicts change in outcomes (symptoms, functioning, rehospitalization) and proposed mechanisms [98]. These exploratory analyses will follow the intent-to-treat principle (i.e., all patients randomized to treatment). Differences in median days to hospitalization between conditions, log-rank test, and preliminary Cox proportional hazards models will be used to understand treatment effects on time to re-hospitalization during follow-up. In addition, the potential magnitude of the indirect effect of condition on outcomes will be explored in a preliminary fashion by testing between-condition differences in mechanisms targeted by the intervention (path ‘a’) (e.g., mindfulness) and determining whether group differences (path ‘b’) are related to outcomes. The product of path coefficients will provide an estimate of the mediation effect and confidence intervals [99]. We acknowledge we will be underpowered for formal mediation testing. However, the partitioning of variance should provide interpretive guidance regarding the effects of ACT-IN mechanisms when assessing symptomatic outcomes.

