**Psychiatric Symptoms**			
Brief Psychiatric Rating Scale (BPRS) [45,82]	Psychiatric symptoms	Interviewer	BL,DC,4
Clinical Outcomes in Routine Evaluation (CORE) [83]	Psychiatric symptoms	Self-Report	BL,DC,4

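### Baseline BPRS is adjusted for only if the arms happen to differ, so the primary comparison is less precise than it could be and depends on the data for its form

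*Protocol article*

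**What the plan says.** Section 3 (Sample Size and Data Analysis Considerations) makes three statements that bear on the point.

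- Outcome: "the primary outcome will be change on the BPRS total scale".
- Model: the analysis is described as "multilevel linear models in a preliminary fashion to examine whether treatment condition, time, and the treatment condition X time interaction predicts change in outcomes". The authors call this preliminary and exploratory, and say it matches what they would do in a later full-scale trial.
- Covariates: "If baseline differences are identified and associated with outcomes, these variables will be used as covariates in subsequent analyses".

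Section 2.9 and Table 1 place the BPRS at baseline, discharge and 4 months. The functioning and mechanism measures follow the same three-visit schedule. Section 3 also says that effect-size standard errors and confidence intervals will be examined, so precision is part of what the pilot is meant to deliver.

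**The concern.** In a randomised comparison, baseline BPRS is useful as a covariate because it correlates with later BPRS. That gain is there whether or not the arms differ at baseline. The stated rule ties adjustment to an observed difference, which under randomisation arises only by chance. When the arms look alike, the adjustment is left out and the precision is lost. When they do not, it is brought in after looking at the data. The form of the primary estimator is therefore settled by the sample and not by the plan.

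Two things are at stake. The pilot's between-arm BPRS intervals would be wider than they need be. The same approach would also pass into the full-scale trial, where lost precision has to be paid for in patients.

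**Working it through.** **Inputs.** From the article: 1:1 allocation (section 2.4), 50 patients in the pilot RCT, so 25 per arm, and an attrition goal below 20% (section 2.11), so about 50 × 0.8 = 40 completers at that limit. Not given: the correlation r between baseline and a later visit, and any BPRS standard deviation. Both are assumed below and varied.

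**The article's own figures.** The power statement is for "80% power to detect group differences at a two-tailed alpha level of .05 over 3 time points", with totals of 526, 86 and 36 for f = 0.10, 0.25 and 0.40. A repeated-measures test of the group effect with m = 3 measurements has noncentrality λ = f²·N·m / [1 + (m − 1)ρ] on 1 and N − 2 degrees of freedom. With ρ = 0.5, which the article does not state:

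- f = 0.10, N = 526: λ = 0.01 × 526 × 3/2 = 7.89, power 0.801
- f = 0.25, N = 86: λ = 0.0625 × 86 × 3/2 = 8.06, power 0.802
- f = 0.40, N = 36: λ = 0.16 × 36 × 3/2 = 8.64, power 0.815

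All three totals are reproduced exactly. With ρ = 0.3 the totals would be 422/70/30, and with ρ = 0.7 they would be 630/104/42. A condition-by-time test at ρ = 0.5 would give 164/28/12. So 0.5 is the one correlation that can be inferred from the article, and three measurements means that baseline is counted among them.

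**Variance with and without adjustment.** Let s0 and s1 be the SDs at baseline and at a later visit. Per patient:

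- change score: s0² + s1² − 2·r·s0·s1
- adjusted for baseline: s1²(1 − r²)
- difference between the two: (s0 − r·s1)², which is never negative

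With s0 = s1 = 1 these become 2(1 − r) and 1 − r², so the ratio of adjusted to change-score variance is (1 + r)/2. The 95% half-width in SD units with 25 per arm is 1.96·√(2V/25).

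| r | V, change | V, adjusted | Variance saving | CI narrower by | Half-width, change | Half-width, adjusted |
|---|---|---|---|---|---|---|
| 0.3 | 1.40 | 0.91 | 35% | 19% | 0.66 | 0.53 |
| 0.5 | 1.00 | 0.75 | 25% | 13% | 0.55 | 0.48 |
| 0.7 | 0.60 | 0.51 | 15% | 8% | 0.43 | 0.40 |

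With 40 completers and r = 0.5 the half-width falls from 0.62 to 0.54 SD.

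A generalised least squares check on three visits with a common correlation compared a free baseline mean in each arm with a baseline mean constrained equal across arms. It gave the same 35%, 25% and 15% at discharge and at 4 months.

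**Unequal SDs.** With k = s0/s1 the saving is (k − r)² / (1 + k² − 2rk).

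| k | r = 0.3 | r = 0.5 | r = 0.7 |
|---|---|---|---|
| 0.7 | 15% | 5% | 0% |
| 1.0 | 35% | 25% | 15% |
| 1.4 | 57% | 52% | 49% |

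**What it would mean in a full-scale trial (illustration).** For a 0.5 SD difference, two-sided 5% and 80% power, n per arm is 88 against 58 at r = 0.3, 63 against 48 at r = 0.5, and 38 against 33 at r = 0.7 (change score against adjusted).

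**The case against.** The strongest reply is that the article never says in words that baseline gets its own mean in each arm. It lists model terms in a condensed account. A change score can itself be analysed with baseline as a covariate, and a fuller plan may do so. This limits what can be said about the exact parameterisation. It does not answer the point, because the article does state a rule for covariates, and that rule makes adjustment conditional on observed imbalance. The rule could bring baseline BPRS in, so it would be wrong to say that the plan never adjusts for it. The fault is that it does so only by chance and after inspection.

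The second reply is that this is an unpowered pilot whose main aim is feasibility, and that a change-score or interaction analysis is valid under randomisation. Both are correct. At r = 0.5, half-widths of 0.55 and 0.48 SD are both too wide to settle efficacy.

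The third reply is that r and the SDs are unknown. This also stands. Section 2.9 uses different rating windows (a week, 24 hours, a week), so equal SDs are doubtful.

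A reader might go further and argue that, with visits so unevenly spaced, a single linear slope would hide an effect at discharge. The article does not say how time is coded, and it expects improvement by discharge, so that argument has no footing in the text.

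**Conclusion.** The point holds as one of efficiency and prespecification. As written, adjustment for baseline BPRS depends on a chance imbalance, and the resulting estimator is less precise than one that always adjusts.

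The direction does not depend on the assumed values, apart from the small cost of estimating one extra parameter. The size does. With equal SDs the variance saving is 25% at the inferred r = 0.5 and 15% to 35% over r = 0.7 to 0.3. With unequal SDs it runs from about 0% to over 50%.

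Two stronger readings should be resisted. The 15% to 35% is not a figure from the article, nor is it a loss in interval width, which is about 8% to 19% on the same assumptions. The documents also give no ground for calling the planned comparison biased or invalid. The point deserves attention because the change is almost free and because the article carries this analysis into the full-scale trial.

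**What to change.** State in section 3 that BPRS total is analysed with its own baseline value as a prespecified covariate, or in a mixed model with a common baseline mean across arms, whatever imbalance is observed. Apply the same form to the functioning and mechanism measures, which are also collected at baseline. Report the adjusted between-arm difference, with its confidence interval, at discharge and at 4 months. Remove the outcome's own baseline value from the conditional covariate rule, so that the rule no longer decides the form of the primary model.

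The cost is wording and code, plus about one degree of freedom. No new data are needed, because Table 1 already schedules these measures at baseline. The article reports the pilot RCT as still recruiting, so the change can be made before outcomes are compared by arm.

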### 2.2. Sample

Participants will be inpatients recruited from Butler Hospital, a 180-bed private, non-profit psychiatric and substance abuse hospital located in Providence, RI. Inclusion criteria include: (1) current psychiatric hospitalization; (2) DSM-5 diagnosis of a primary psychotic disorder or mood disorder with psychotic features (schizophrenia, schizoaffective disorder, schizophreniform, delusional disorder, psychotic disorder unspecified, bipolar disorder with psychotic features, major depressive disorder with psychotic features) as determined by structured clinical interview [48]; (3) 18 years or older; and (4) ability to speak and read English. Exclusion criteria include: (1) psychosis severe enough to prevent participation in regular hospital therapy groups; (2) psychosis related to a general medical condition or substance-induced psychotic disorder; or (3) severe cognitive impairment (Mini-Mental State Exam < 15) [49].

We chose to include patients with schizophrenia-spectrum disorders, including psychotic mood disorders, as the treatment is designed to be applicable to patients with a wide range of symptoms. Patients will likely display a range of severity and treatment will be tailored to higher and lower functioning patients. Based on our pilot work [44], patients judged by their psychiatrist to be stable enough to participate in routine group therapy will be eligible to participate in the study. Typically, patients are encouraged to begin attending hospital groups when they are stabilized enough on medications to remain in the group setting without disruption (within first 1–2 days after admission). Patients will not be excluded due to negative symptoms (e.g., flat affect), but will be excluded if determined to exhibit severe cognitive impairment due to potential difficulty participating in research. Mild to moderate cognitive impairment will be permitted.

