### 2.9. Assessments

Assessments will be conducted shortly after hospital admission (baseline), at hospital discharge (or shortly thereafter for unexpected discharges), and 4 months post-discharge (as done in the initial ACT inpatient studies). At admission, clinical interviews will assess the week immediately preceding hospitalization, the discharge assessment will assess current severity/functioning (past 24 h), and the follow-up assessment will assess the previous week. We will assess diagnosis, psychiatric symptom severity including psychosis, psychosocial functioning and quality of life, treatment adherence and utilization (including rehospitalization rates at follow-up), treatment satisfaction and acceptability, and the proposed mechanisms of ACT-IN (mindfulness, acceptance, values). Severity of positive and negative symptoms will be assessed using the relevant subscales from the BPRS, which have demonstrated reliability and validity for this purpose [81]. A list of measures with a brief description of each is provided in Table 1.

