**Treatment Adherence/Utilization**			
Brief Adherence Rating Scale (BARS) [87]	Medication adherence	Interviewer	4
Treatment History Interview-4 (THI-4) [88]	Treatment utilization	Interviewer	4

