**Acceptability/Satisfaction**			
Client Satisfaction Questionnaire-8 (CSQ-8) [91]	Treatment satisfaction	Self-report	DC
Qualitative Post-Treatment Interview	Treatment satisfaction	Interview	DC

Note: BL = Baseline, DC = Discharge, 4 = 4 Month Follow-up.

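### Rehospitalisation is listed under the condition-by-time multilevel linear model, but it is assessed only at the 4-month follow-up, so the time and interaction terms cannot be estimated for it

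*Protocol article*

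**What the plan says.** Section 3 (Sample Size and Data Analysis Considerations) of the protocol article plans multilevel linear models whose terms are condition, time and their interaction. It asks whether each of these "predicts change in outcomes (symptoms, functioning, rehospitalization) and proposed mechanisms". Rehospitalisation is thus expressly assigned to this model, next to symptoms and functioning.

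The data that would feed the model are described elsewhere in the article:

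- Section 2.9 (Assessments) lists treatment utilisation among the domains, "including rehospitalization rates at follow-up".
- Table 1 gives the utilisation interview, the THI-4, with time point 4 only. The table note reads "BL = Baseline, DC = Discharge, 4 = 4 Month Follow-up". The symptom, functioning and mechanism measures are scheduled at all three points.
- Section 2.2 (Sample) opens its criteria with "Inclusion criteria include: (1) current psychiatric hospitalization".

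Section 3 also names rehospitalisation rates as a secondary outcome. Later in the paragraph that contains the multilevel models, it plans median days, a log-rank test and preliminary Cox models for time to rehospitalisation.

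**The concern.** A multilevel model with condition, time and their interaction describes how an outcome measured repeatedly in the same patient changes, and whether that change differs by arm. It needs at least two measured values per patient. Rehospitalisation, as the article describes its collection, has one.

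Followed literally, the sentence leads to one of two results. Either the software drops or rejects the time terms and the planned estimate does not exist, or the analyst supplies zeros at baseline and discharge to make the model run and obtains a standard error that is too small.

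The article describes these models as the kind it would use in the later full-scale trial, and specifying procedures for that trial is a stated purpose of the project. An unworkable model left in the plan could therefore be carried forward.

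**Working it through.** The article gives no figure of its own for this analysis, so there is none to reproduce. The check has two parts.

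**1. Can the model be estimated with the data as described?**

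Inputs: 50 patients in the pilot RCT (section 2.1); 1:1 allocation (section 2.4), hence 25 per arm; model terms from section 3; assessment times from Table 1.

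Each row of the fixed-effect design is [1, condition, time, condition × time].

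- *Outcome at month 4 only.* There are 50 rows. Time takes a single value c in every row, so the time column is c times the intercept column, and the interaction column is c times the condition column. Rank is 2, against 4 parameters. With time as a three-level factor, rank is 2 against 6. Only the contrast between arms at month 4 is identified.
- *Outcome at baseline, discharge and month 4 (BPRS, WHODAS and similar).* There are 150 rows. Rank is 4 of 4 with linear time and 6 of 6 with time as a factor. The model suits these outcomes.

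With one row per patient, the random-intercept variance also cannot be separated from the residual variance. None of this depends on the coding. One count, or one number of days in hospital, per patient gives the same design matrix.

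**2. What happens if baseline and discharge are filled with zeros?**

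Assumptions: the outcome is coded 0/1; the 4-month proportions are 20% and 40%, the rates that section 1 (Background) reports from the first randomised trial of ACT in inpatients; 25 per arm with no loss to follow-up, hence 5 and 10 events; time is a factor.

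- Interaction estimate (month 4 versus baseline): 0.20 − 0.40 = −0.20.
- All residual variation sits at month 4: 25 × 0.2 × 0.8 + 25 × 0.4 × 0.6 = 4 + 6 = 10.
- Pooled residual variance: 10 / (150 − 6) = 0.0694.
- A random intercept does not change this. The between-patient mean square is (10/3)/48 = 0.0694 and the within-patient mean square is (20/3)/96 = 0.0694, so the estimated intercept variance is zero.
- SE of the interaction: √(0.0694 × 4/25) = 0.105. The 95% CI is −0.20 ± 1.96 × 0.105, or −0.41 to +0.01.
- Direct comparison at month 4: SE = √(0.2 × 0.8/25 + 0.4 × 0.6/25) = √0.016 = 0.126. The 95% CI is −0.45 to +0.05.
- Ratio: √(0.0111/0.016) = 0.83.

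The two estimates are identical, but the zero-filled model reports an SE about 17% too small. The 100 structural zeros have no variance, and they dilute the pooled residual.

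**The case against.** The strongest reply is that one interview date need not mean one datum. Median days and Cox models require dated admissions, so dates within the 4 months must be collected, and these could be split into intervals and modelled repeatedly. A condensed article may leave such variable construction to the full protocol. This stands as a possibility, and it is why the point is limited to the data as described. The article sets out no interval structure, however, and its sentence treats rehospitalisation in the same way as outcomes measured at baseline, discharge and month 4.

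A second reply is that suitable methods are already there. The same paragraph plans log-rank and Cox analyses, and section 3 promises confidence intervals and number needed to treat. This also stands and lowers the severity. But nothing says that those methods replace the multilevel model for rehospitalisation.

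Three stronger readings are tempting, and the document does not support them:

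- A reader might infer that rehospitalisation is a single yes/no variable. The article speaks of rates and never states the coding. The identifiability problem does not need that assumption; only the zero-filling illustration does.
- A reader might infer that the plan holds two contradictory analyses of one outcome. A rate and a time to event are different summaries, and analysing both is legitimate. The fault is one unsuitable model.
- A reader might take the wide interval for the risk difference (−45 to +5 percentage points) as the size of the defect. It shows only the imprecision of 25 per arm, and it would be the same whichever way the sentence were worded.

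**Conclusion.** The point holds in this form: section 3 assigns rehospitalisation to a model whose time and interaction terms are not estimable from one value per patient, and one value at the 4-month follow-up is all that the article describes. This is a rule stated wrongly, and not a detail left out.

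The consequence is limited. The models are called preliminary and exploratory, the project's main objective is feasibility and acceptability, rehospitalisation is a secondary outcome, and the BPRS primary outcome has three assessments and is unaffected. If the model is run on one row per patient, the failure will be obvious. The quieter risk is zero-filling, which under the assumed 20% versus 40% with 25 per arm understates the standard error by about 17% (0.105 against 0.126). That figure depends on the assumed proportions, 0/1 coding, complete follow-up and time as a factor. The rank result depends only on there being one value per patient.

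**What to change.** Delete rehospitalisation from the list of outcomes for the multilevel linear models, leaving symptoms, functioning and mechanisms. Add one clause: the proportion rehospitalised by the 4-month follow-up will be compared between arms as a risk difference with its 95% confidence interval. Keep the log-rank and Cox analyses of time to rehospitalisation as written. Adjustment for the randomisation strata is a separate choice, and this point does not require it.

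The cost is one word removed and one clause added. Sample size, visits and data collection do not change.

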## 1. Background

Schizophrenia-spectrum disorders (SSD), such as schizophrenia and psychotic mood disorders, are frequently disabling illnesses present in approximately 3.5% of the general population [1]. Schizophrenia is among the top 10 leading causes of disability worldwide [2], and the most disabling psychiatric disorder [3]. In 2002, the total estimated cost of schizophrenia alone in the U.S. was $62.7 billion, with $22.7 billion in direct treatment costs [4]. Patients with SSD represent 25–38% of psychiatric hospital admissions [5,6,7,8]. These patients frequently require hospitalization for safety issues [9,10]. Recurrent inpatient admissions, which are often required during the acute phase of illness for crisis management and stabilization, are key determinants of the high costs of SSD [11]. Reducing relapses and preventing rehospitalizations are important treatment priorities for the management of persons with SSD.

The post-discharge period is a time of increased risk associated with a host of negative outcomes [12,13,14,15]. For example, a Danish study showed that suicide rates were highest within the first 5 days post-discharge and increased with multiple admissions [12]. In addition, research shows that only 50% of patients with SSD achieve functional and symptomatic recovery by 6 months post-hospitalization and many fail to maintain it [16]. In another study of 76 hospitalized patients with schizophrenia, 38% were rehospitalized at least once over 18 months [17]. Frequent hospitalizations cause significant disruptions to patients’ lives. Also, inpatients are at heightened risk for treatment nonadherence following discharge [18] and nonadherence is predicted by inadequate discharge preparation [19,20]. Thus, patients with SSD are at high risk for subsequent relapse and rehospitalization following an acute hospitalization.

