Recently, psychosis researchers have begun investigating innovative new forms of CBT that emphasize acceptance (i.e., willingness to experience unavoidable psychological distress) and mindfulness (i.e., nonjudgmental, present-moment attention) strategies [24,33]. The only form of CBT for psychosis that has been tested in randomized controlled trials in short-term hospital settings in the U.S. to date is called Acceptance and Commitment Therapy (ACT). ACT is a newer form of CBT that emphasizes acceptance and mindfulness instead of challenging the content of dysfunctional thoughts (i.e., cognitive restructuring), and focuses on behavior change strategies guided by the patient’s personal values to improve functioning and coping with persistent symptoms [34]. ACT is currently listed as an empirically-supported psychotherapy by the American Psychological Association [35] for a number of psychiatric conditions, including psychosis, and is further recognized by the U.S. Substance Abuse and Mental Health Services Administration [36] and U.S. Veterans Administration [37]. Recent meta-analyses demonstrate that ACT is at least as effective as more traditional forms of CBT and is efficacious in terms of both acute and longer-term effects on symptoms and functioning for a wide variety of conditions, including psychosis, borderline personality disorder, chronic health conditions (e.g., pain, epilepsy, diabetes), substance abuse, depression, and anxiety disorders [38,39,40]. Finally, a recent meta-analysis focused specifically on early mindfulness and acceptance therapies for psychosis, including ACT, showed medium effect size improvements on positive and negative symptom outcomes through follow-up compared to comparison conditions, and changes in mindfulness and acceptance predicted changes in symptoms [41].

As mentioned, previous research shows that ACT is feasible and efficacious for treating psychosis specifically in acute-care hospital settings. In the first randomized controlled trial conducted in a mixed sample of 80 inpatients with SSD, Bach and Hayes [42] found that a brief, 4-session, individual ACT intervention reduced the believability of psychotic symptoms and rates of rehospitalization (20% vs. 40%) over 4 months post-discharge compared to a TAU condition. The advantage for ACT over TAU in terms of rehospitalization rate was maintained at 1 year follow-up [43].

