### 2.11. Retention Efforts

Our goal will be to achieve <20% attrition over the course of the study. However, we will assess whether attrition is higher than expected and use this information to determine feasibility and sample size needed for a future large-scale clinical trial. Subjects will be compensated for completing assessments ($25 each for the admission and discharge assessments, and $50 for the follow-up assessment). Assessors will phone patients periodically during follow-up to maintain contact and update information. Cab rides/bus passes will be provided for subjects unable to transport themselves to our center for their follow-ups. We will attempt to continue to collect assessment data even if patients withdraw from the study.

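### The planned difference in median days to rehospitalisation is very unlikely to be estimable within a 4-month follow-up

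*Protocol article*

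**What the plan says.** Section 3 of the protocol article (Sample Size and Data Analysis Considerations) names "Differences in median days to hospitalization between conditions" as one of three analyses of this outcome. The other two are a log-rank test and Cox models. The stated purpose of all three is "to understand treatment effects on time to re-hospitalization during follow-up". Section 2.9 places the last assessment at "4 months post-discharge (as done in the initial ACT inpatient studies"), so observation of this outcome ends there. Section 3 gives the pilot's size, "with an open trial sample of 20 and a pilot RCT sample of 50", and Section 2.4 allocates 1:1, which makes 25 patients per arm.

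The article states no expected rehospitalisation rate for its own two arms. The Background cites two rates from other studies. An earlier randomised trial of ACT in 80 inpatients found reduced "rates of rehospitalization (20% vs. 40%) over 4 months post-discharge compared to a TAU condition". In a cohort of 76 hospitalised patients with schizophrenia, "38% were rehospitalized at least once over 18 months". Rehospitalisation rates are also listed in Section 3 as a secondary outcome.

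**The concern.** The Kaplan-Meier median is the time at which the estimated event-free proportion reaches 50%. If fewer than about half of an arm are rehospitalised during follow-up, the median lies beyond the data and is reported as not reached. A difference in medians needs both arms to pass 50%. Every rehospitalisation rate in the article is below 50%, including the one over 18 months, while the window here is 4 months. The article names no substitute for the case where the median is not reached.

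At stake is the one planned summary of this outcome on a time scale in days. The pilot exists to settle procedures for a full trial, and a larger sample would not cure the problem. With the same 4-month window and true risks below 50%, the chance of reaching the median shrinks as the sample grows.

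**Working it through.** The article gives no figure for median time to rehospitalisation, so there is nothing of its own to reproduce. The check asks whether the named summary can exist under the rates that the article cites.

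**Inputs**
- Patients per arm: 50 / 2 = 25 (Sections 2.4 and 3).
- Follow-up: 4 months (Section 2.9), taken as 120 days.
- 4-month rehospitalisation risk: 20% and 40% (Background, earlier ACT trial).
- Other rate: 38% over 18 months (Background, separate cohort).
- Attrition: the goal is below 20% (Section 2.11).

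**Step 1. Expected position of the curves at month 4.** Event-free proportion = 1 − risk, which gives 1 − 0.20 = 0.80 and 1 − 0.40 = 0.60. Neither has reached 0.50.

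**Step 2. Chance that an arm reaches its median.** With complete follow-up, at least 13 of 25 patients must be rehospitalised. The chance is P(X ≥ 13) with X ~ Binomial(25, p):

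| 4-month risk p | P(X ≥ 13) |
|---|---|
| 20% | 0.0004 |
| 30% | 0.0175 |
| 40% | 0.154 |
| 45% | 0.306 |
| 50% | 0.500 |

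**Step 3. Chance that both medians exist.** At 20% and 40%: 0.000369 × 0.1538 = 0.00006, or about 0.006%.

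**Step 4. Allowing for dropout.** A simulation of 20,000 arms per setting, with constant hazards and 20% random dropout, gave 0.04% and about 17% for the two arms. The chance for both was 0.0004 × 0.1687 = 0.00007, still below 0.01%.

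**Step 5. Sensitivity to the cited rates.**
- 38% over 18 months, at a constant hazard (assumption): 1 − 0.62^(4/18) = 10.1% at 4 months. The Background describes the period after discharge as one of raised risk, so this may be too low.
- As an upper limit, suppose that all 38% fell within the first 4 months in both arms. Each arm would reach its median with probability 0.109, and both with 0.109 × 0.109 = 0.012.
- At a true 4-month risk of 50% in both arms, above any rate in the article, both would do so with probability 0.5 × 0.5 = 0.25.

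**Step 6. Where the medians would lie.** With constant hazard h = −ln(1 − p)/120 (assumption), the median is ln 2 / h:
- 20%: h = 0.2231/120 = 0.001860 per day, median about 373 days.
- 40%: h = 0.5108/120 = 0.004257 per day, median about 163 days.

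Both lie beyond day 120.

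**Step 7. What remains estimable.** Expected events are 25 × 0.20 + 25 × 0.40 = 15. The implied hazard ratio is ln 0.80 / ln 0.60 = 0.44. Log-rank and Cox can be computed, with about 36% power by Schoenfeld's formula. Restricted mean time to first rehospitalisation up to day 120 is (1 − e^(−120h))/h:
- 20%: 0.20 / 0.001860 ≈ 107.6 days.
- 40%: 0.40 / 0.004257 ≈ 94.0 days.

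The difference is about 13.6 days, and the risk difference is 20 percentage points.

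**The case against.** The strongest reply is that little depends on the median. The same sentence plans a log-rank test and Cox models, neither of which needs it. Section 3 also lists rehospitalisation rates as a secondary outcome and commits to effect sizes with confidence intervals and measures such as number needed to treat. The pilot is deliberately unpowered, its primary objective is feasibility and acceptability, and these analyses are labelled exploratory. A median shown as not reached misleads nobody. This stands, and it limits the impact. A reader might infer that the pilot would hand the full trial no usable effect measure for rehospitalisation. The article does not support that.

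Second, 20% and 40% are another trial's results, not rates assumed for these arms. This also stands. They are, however, the only 4-month rates in the article, they come from the same follow-up length, and Step 5 shows that the conclusion does not need them to be exact.

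Third, an analysis plan may name a fallback. That is possible, but the point is not an omission: the article names a summary that fits poorly with its own follow-up length and cited rates.

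A reader might also suspect that the median is meant among rehospitalised patients only, which would compare groups selected by the outcome. Nothing in Section 3 says so, and the intent-to-treat statement just before the sentence points the other way.

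**Conclusion.** The concern holds in a limited form. Under the cited 4-month rates, the difference in medians would be estimable in fewer than 1 in 10,000 trials of this size. It is therefore very unlikely to be available, though not strictly impossible. It would be too strong to say that neither arm can reach its median: an arm with a 40% risk would do so by chance in about 15% of trials. It is the difference that is practically excluded.

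The binomial result rests on 25 patients per arm, complete 4-month follow-up and true risks near those cited. The medians in days, the restricted means and the simulation also assume constant hazards, which the article does not state. The consequence is confined to the only summary in days for an exploratory secondary outcome. Because the correction is cheap and the pilot's methods are meant to carry into the full trial, it is worth making now.

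**What to change.** In Section 3, replace the difference in median days with two summaries, each with a 95% confidence interval and computed on all randomised patients:

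- the difference in restricted mean time to first rehospitalisation up to 4 months (day 120);
- the difference in Kaplan-Meier 4-month rehospitalisation risk.

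Keep the log-rank test and Cox models as planned. The restricted mean should be labelled as time to first rehospitalisation. Days spent out of hospital is a different quantity, because it depends on the length and number of readmissions.

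The cost is a line of analysis text and minor extra analysis work, with no change to design, sample size, assessments or treatment. The drawback is that the restricted mean is tied to the 4-month horizon and cannot be compared directly with studies that use another one.
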